## Abstract

**Background:**

Diabetes self-management is a mainstay of diabetes care, but the implementation of self-management regimens into daily life is complex and often results in discouragement and distress. Modern approaches such as smartphone-based self-management applications are therefore needed to support people with diabetes. Since reimbursability would increase the availability of such digital applications to people with diabetes, we designed a study that meets all scientific and methodological requirements set by the German Digital Healthcare Act to allow reimbursement for a specific application (mySugr PRO). Here, we report the protocol of this study that aims at evaluating the efficacy of the digital self-management application with regard to patient-reported outcomes and medical benefits.

**Methods/design:**

This multicenter, open-label, randomized, parallel-group, controlled trial will evaluate the health care effects and medical benefits of mySugr PRO. A total of 466 people with diabetes will be randomly allocated (2:1 randomization) to the interventional group (*n* = 311) that will use the digital self-management application during the 12-week study period or the control group (*n* = 155; no usage of the application). Baseline and follow-up examinations will assess diabetes distress as the primary endpoint as well as empowerment, HbA1c, blood glucose data, self-management, general well-being, and treatment satisfaction as secondary endpoints. Statistical analyses will use an intention-to-treat procedure (using multiple imputation for missing values) as well as a per-protocol approach for sensitivity analysis.

**Discussion:**

To the best of our knowledge, this study will be one of the largest diabetes-specific evaluations of a digital health application supporting people with diabetes in their diabetes self-management that follow the requirements of the German Digital Healthcare Act.

**Trial registration:**

German Clinical Trial Register DRKS00022923. Registered on 22 October 2020.

## Background

Diabetes self-management, the active engagement in a healthy lifestyle and preventive behaviors, is a mainstay of diabetes care. In addition to regular glucose monitoring and treatment adherence, self-management includes the careful planning of diet and physical activities as well as coping with low and high glucose levels [1, 2]. An effective diabetes self-management helps to maintain tight glycemic control and, thereby, to reduce the risk for diabetic complications [3–5]. However, the implementation of diabetes self-management regimens into daily life can be complex and demanding, leading to discouragement and distress [6]. Diabetes-related distress has been proven associated with compromised diabetes self-care [7], reduced health‐related quality of life [8], and impaired glycemic control [9, 10]. Approximately one-third of people with diabetes suffer from elevated diabetes distress [11–13]. This underlines the need for strategies and interventions to support the self-management of people with diabetes [2, 14].

Since people with diabetes are commonly facing constantly changing internal and external influences affecting their glucose levels, tools to support diabetes self-management are required to be permanently accessible to patients. Therefore, digital applications are increasingly employed for diabetes care [15], and meta-analyses demonstrated the beneficial effects of digital applications on weight development, treatment adherence [16], diabetes distress [17], and HbA1c levels in people with diabetes [18, 19].

Reimbursability would make digital applications for diabetes self-management more widely available. In Germany, the Digital Healthcare Act (2019; [20]) requires digital applications applying for reimbursement to be listed in an official register maintained by the German Federal Institute for Drugs and Medical Devices (BfArM), as reviewed by Gerke et al. [21]. To be listed, digital applications need to demonstrate one or more positive health care effects. For diabetes care, these effects could comprise direct medical benefits (glucose, HbA1c, quality of life) and other patient-relevant improvements such as reduced diabetes distress and increased treatment adherence. Methodically, the evaluation of positive health care effects requires a retrospective or prospective comparative study demonstrating better outcomes in patients using the relevant digital application than in patients not using it [21].

One digital health application for people with type 1 or type 2 diabetes is the mySugr PRO app. It was developed in accordance with the requirements for quality management systems for medical devices [22] and has been shown to be positively associated with higher self-care behavior [23]. Data assessed by the app include current glucose levels (automatic upload from monitoring devices is possible), estimated HbA1c (eHbA1c) values, data on medication/insulin intake, and entries on diet, weight, blood pressure, and activity. To add individual context to these medical data, additional information on, for example, time, location, and stress level (general stress, disease) can be entered. Users are then presented with analyses on the eHbA1c and the percentages of hypo- and hyperglycemic values. Traffic light colors indicate critical glucose data, and algorithms for pattern detection identify areas where self-management should be improved. Importantly, concepts known from behavioral psychology such as challenges and direct positive feedback are integrated to foster motivation [24, 25].

As required by the BfArM guidance document [26], a retrospective systematic analysis of glucose metrics from German-speaking app users including a comparison of the app users with a historical cohort of non-users was conducted beforehand to justify the assumed clinical benefits on glycemic control and diabetes distress that are to be confirmed by this study [27]. A more sophisticated study is now required for reimbursement purposes by the BfArM.

Here, we report the study protocol of a parallel, randomized, controlled study to assess the efficacy of the digital health application for diabetes self-management. Efficacy will be assessed via patient-reported outcomes and medical benefits. Study endpoints will comprise the reduction of diabetes distress after 12 weeks (primary endpoint) as well as effects on self-management and treatment adherence, empowerment, self-efficacy, treatment satisfaction, and clinical changes of HbA1c, blood glucose, and quality of life. This study was designed to meet all requirements set by the Digital Healthcare Act and is being conducted between October 2020 and August 2022 in approximately 50 diabetology centers in Germany.

## Method/design

### Study design

This study is a multicenter, open-label, randomized, parallel-group, controlled trial to evaluate the health care effects and medical benefits of a smartphone-based self-management app. In the interventional group, people with diabetes will use the mySugr PRO app as a digital health application during the 12-week study period. The app aims at supporting people with diabetes in their day-to-day self-management but makes no treatment recommendations. The functions of the intervention are summarized in Table 1. In the control group, people with diabetes will continue with their usual mode of therapy, data documentation, and glucose monitoring.

**Table 1 Tab1:** Summary of mySugr PRO functions

Category	mySugr PRO functions
Data entry	Blood glucose (self-monitored blood glucose [upload], HbA1c) Medication (insulin, other medications) Health data (diet, weight, blood pressure, activity) Context data (time, location, well-being, pictures)
Analysis	Time-course of blood glucose levels Estimated HbA1c (eHbA1c) Hypo- and hyperglycemic episodes Critical glucose data (traffic light colors) Areas for self-management improvement
Motivation	Blood glucose monitoring reminder Game-mechanics: challenges Direct positive feedback loops on self-management success
Patient-physician interaction	Statistics and detailed logs in different data formats

Approximately 50 study centers will take part in this study with approximately 9 participants each. The primary endpoint is the reduction of diabetes distress after 12 weeks. Secondary endpoints comprise diabetes self-management, empowerment, general well-being, self-efficacy, treatment satisfaction, and blood glucose and HbA1c levels. As an additional outcome measure, the real-life experience (e.g., daily helpfulness) of the investigational group will be evaluated by using the ecological momentary assessment (EMA, [28]). The study protocol was prepared in accordance with the checklist for protocols of interventional studies [29] and the DIN standard for the clinical investigation of medical devices for human subjects [30]. The SPIRIT reporting guidelines have additionally been applied [31]. The Ethics Committee of the Medical Chamber of Baden Württemberg has approved the Clinical Investigation Plan of the study on 22 October 2020 (FI-A-1–2020). The study is registered at the German Clinical Trial Register (DRKS00022923).

In sum, the study is designed to evaluate three hypotheses: Compared to a treatment-as-usual control group, the smartphone-based diabetes self-management app is effective in the following:Reducing diabetes distressImproving glycemic controlImproving other patient-reported outcomes indicating improved diabetes management

### Study population

People diagnosed with type 1 diabetes (ICD-10 code E10), type 2 diabetes (ICD-10 code E11), or gestational diabetes (ICD-10 code O24.4) are eligible for this study. The inclusion criteria further comprise the capability for both daily blood glucose measurements and corresponding adjustment of therapy, age ≥ 16 years, last obtained HbA1c value < 12% (107.6 mmol/mol), possession of a smartphone compatible with the intervention (Android ≥ 5.0; iOS ≥ 11.4), willingness to accept terms of conditions of the app, German language skills, and provision of informed consent. Patients will be excluded if they are currently using continuous glucose monitoring (CGM) systems (real-time and intermittently scanned CGM), if they used digital diabetes diaries or digital applications for therapy documentation in the last 3 months before study entry, if they have any medical conditions contradicting with diabetes therapy and study participation, or if they are simultaneously participating in another clinical trial.

For the primary outcome, the calculation of the intended sample size was based on the assumption of an expected effect size of 0.3 standard deviations. Statistically, this assumption was derived from a previous analysis evaluating the effect of the digital health application on diabetes distress [27]. Clinically, this effect size was chosen to allow interpretation of clinically meaningful effects as effect sizes below 0.3 have limited implications for clinical practice. Employing a 2:1 randomization, power analysis revealed that 396 participants would be required to achieve a power of 1 − *β* = 0.80 with a two-sided *α* error of 0.05. With an assumed drop-out rate of 15%, we intend to recruit 466 participants (311 intervention, 155 control). Drop-out will be defined as participants who completed baseline assessment of the primary endpoint but were lost to follow-up or withdrew informed consent.

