### Statistical analysis

All evaluations on positive care effects will base on intention-to-treat analyses. Missing values will be identified and replaced by using multiple imputation [40]. Additional sensitivity analysis will be performed with the per-protocol population. Descriptive data will be presented as absolute and relative frequencies (categorical, nominal data), median and interquartile range (75% percentile and 25% percentile; ordinal data), and mean ± SD (interval-scaled variables). The differences between the interventional and control groups will be assessed by the analysis of covariance with baseline data as a covariate, and follow-up data and group membership as dependent and independent variables, respectively. To control for multiplicity, analysis of primary and secondary endpoints will be carried out using a hierarchical testing approach with the following sequence: PAID, HbA1c, DSMQ, DES, percentage of hypoglycemic blood glucose values, number of blood glucose measurements per day, percentages of euglycemic and hyperglycemic values, average blood glucose levels, GSE, WHO-5, and DSat. For statistical analysis, SPSS 25 and Systat 12 will be used. All data will be treated confidentially and stored in pseudoanonymized form, anonymized when possible, and deleted after the end of the study. [name] will have access to the final trial dataset and will be responsible for analyses.

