As outcome measures, we will not only assess the direct medical effects on blood glucose and HbA1c levels because of their relationship with diabetic complications [43, 44] but also several PRO assessing psychological aspects of diabetes that have been shown to be important to people with diabetes [45, 46]. Preliminary evidence for the beneficial effects of mySugr on specific PRO was obtained in a retrospective systematic analysis, which was conducted during the application process for the Digital Healthcare Act. In this study, the comparison of 1099 study participants using the app with a historical cohort of 824 non-users revealed significantly decreased PAID-5 scores in app users with type 1 or type 2 diabetes (overall sample, 6.32 ± 4.36 vs. 5.07 ± 4.20, *t*(1921) = 6.36, *p* < 0.001; type 1 diabetes, 6.55 ± 4.30 vs. 5.12 ± 3.96, *t*(815) = 4.85, *p* < 0.001; type 2 diabetes, 6.01 ± 4.42 vs. 4.96 ± 4.23; *t*(1066) = 3.75, *p* < 0.001) [27]. Therefore, diabetes distress will be evaluated as the primary endpoint by the PAID questionnaire [33], a widely accepted scale to assess diabetes distress, since its results are associated with the functionality of coping styles, quality of life, and the occurrence of depressive symptoms [47]. Diabetes distress is common among people with diabetes, with a prevalence of approximately 20 to 40% [48, 49] and 36%, respectively [12]. Diabetes distress hinders the optimal management of diabetes and impacts on the emotional well-being, self-care, and quality of life of people with diabetes [13, 50] and, therefore, represents an important and valid outcome measure [51–53]. The broad spectrum of secondary endpoints then aims at reflecting the complexity of diabetes therapy and care that includes the self-management of dietary control, physical activity, and health care use, as well as diabetes-specific empowerment, self-efficacy, and satisfaction with current treatment. There is a great body of evidence that corresponding PRO are clinically relevant as they are associated with glycemic parameters [54], which is particularly true for PRO measures such as diabetes distress and self-management behaviors [13, 47, 50, 55].

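### Gestational diabetes is eligible although the app and the type-specific planning results cover only type 1 and type 2; pooling it without a term for type can cost precision and may dilute the primary effect

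*Protocol article*

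**What the plan says.** Three diabetes types may enter the trial. After type 1 and type 2, the Study population section adds "or gestational diabetes (ICD-10 code O24.4) are eligible for this study". The article gives no reason for this and no expected share or cap. The Background introduces the product more narrowly: "One digital health application for people with type 1 or type 2 diabetes is the mySugr PRO app".

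The sample size is "based on the assumption of an expected effect size of 0.3 standard deviations", and "this assumption was derived from a previous analysis evaluating the effect of the digital health application on diabetes distress". The Discussion describes the PAID-5 data from that source as "the comparison of 1099 study participants using the app with a historical cohort of 824 non-users". It reports "significantly decreased PAID-5 scores in app users with type 1 or type 2 diabetes", with figures for the overall sample, type 1 and type 2. No gestational result is shown.

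Under Procedures, every participant has one baseline visit and one follow-up visit at the end of a 12-week period. The randomisation section mentions blocks but no stratification by diabetes type. The Statistical analysis section states the model as "analysis of covariance with baseline data as a covariate, and follow-up data and group membership as dependent and independent variables, respectively".

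**The concern.** The enrolled population is wider than both the population the app is described for and the types with a reported planning effect. The added type also fits the schedule poorly. Gestational diabetes is tied to pregnancy, and a fixed 12-week interval can run past delivery. PAID, HbA1c and glucose at the second visit may then describe a different state from baseline, in both arms and whatever the app does. HbA1c stands second in the testing hierarchy, and the Discussion says it reflects the preceding 8 to 12 weeks, so a value taken after delivery could mix the two states.

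Two separate losses are possible:

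- **Precision.** Outcome change that depends on type goes into the residual if the model has no term for type.
- **Dilution.** If the app effect is smaller in gestational diabetes, the pooled effect is smaller than in type 1 and type 2 alone. The margin is thin, because the Study population section itself regards effects under 0.3 SD as of limited clinical use.

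A positive pooled result could also be read as covering gestational diabetes, although that group may be far too small to support this.

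**Working it through.** **1. Reproduce the plan's figures.** Inputs from the Study population section: d = 0.3, 2:1 allocation, two-sided α = 0.05, power 0.80, drop-out 15%. The two-sample t-test needs 131.46 controls, rounded up to 132, plus 264 on the app: 396, with power 0.802. Then 396 / 0.85 = 465.9, rounded up to 466. Both stated figures reproduce.

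**2. Planning effect.** The Discussion gives "overall sample, 6.32 ± 4.36 vs. 5.07 ± 4.20". The difference is 6.32 − 5.07 = 1.25 and the pooled SD (824 non-users, 1099 users) is 4.27, so d = 1.25 / 4.27 = 0.293, in line with 0.3. By type, with the root mean square of the two SDs:

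- Type 1: 1.43 / 4.13 = 0.35
- Type 2: 1.05 / 4.33 = 0.24

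The degrees of freedom give 817 people with type 1 and 1068 with type 2, together 1885. The overall sample is 1921 + 2 = 1923, so 38 people (2.0%) are in neither reported group. Their type is not stated.

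**3. Dilution of the pooled effect.** Let g be the gestational share and d_G the app effect in that group. The article gives neither, so both are assumed. The pooled effect is d = 0.3 × (1 − g) + d_G × g. Power is from the noncentral t distribution at 132 and 264, with noncentrality d × √(132 × 264 / 396) = d × √88.

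| Share g | d_G = 0 | d_G = 0.15 | d_G = 0.30 |
|---|---|---|---|
| 5% | d 0.285, power 76.0% | d 0.2925, 78.1% | d 0.30, 80.2% |
| 10% | d 0.270, power 71.5% | d 0.285, 76.0% | d 0.30, 80.2% |
| 20% | d 0.240, power 61.3% | d 0.270, 71.5% | d 0.30, 80.2% |

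If the effect were larger in this group (0.45 SD), a 10% share would raise power to 83.8%.

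**4. Effect of baseline adjustment.** The table is unadjusted, like the plan's own calculation. With an assumed baseline to follow-up correlation ρ, the effect is divided by √(1 − ρ²). At ρ = 0.5, power is 90% for d = 0.30, 83% for 0.27 and 74% for 0.24.

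**5. Precision from a term for type.** Suppose gestational participants shift by s SD relative to the others for reasons unrelated to the app. At g = 10% the variance between types is 0.1 × 0.9 × s² = 0.09 s². With ρ = 0.5 the remaining residual variance is 1 − 0.25 = 0.75. The portion that a type term absorbs is:

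- s = 0.3: 0.0081 / (0.75 + 0.0081) = 1%
- s = 1.0: 0.09 / (0.75 + 0.09) = 11%

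**6. The gestational group alone.** With n_c = 132 × g controls and twice as many on the app, the 95% half-width is 1.96 × √(1/n_c + 1/(2 n_c)). For shares of 2, 5, 10 and 20% of 396 (about 8, 20, 40 and 79 people), power at 0.3 SD is 6, 9, 14 and 24%, and the half-width is 1.48, 0.93, 0.66 and 0.47 SD.

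**The case against.** The strongest reply is that a reader might infer that pooling does dilute the primary effect. The document does not support that. Dilution needs both a material gestational share and an effect below 0.3 SD in that group, and neither is given. With an equal effect there is no loss, and the figures for zero effect are one edge of a range. The planned analysis also adjusts for baseline; at ρ = 0.5, a 10% share with no effect would still leave 83% power. All of this stands.

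Other points also stand:

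- Omitting type does not bias a randomised comparison, and a main effect for type does not undo dilution. It serves precision only.
- It would be too strong to say that all planning data come from type 1 and type 2, because 38 of 1923 people are unaccounted for.
- The prior data do not show that the effect varies by type. The standard errors are 1.43 / 4.85 = 0.295 and 1.05 / 3.75 = 0.280. The gap is 0.38 with standard error √(0.295² + 0.280²) = 0.41, so z = 0.93 and p is about 0.35.
- The article announces no conclusion specific to gestational diabetes. Its hypotheses and conclusion concern people with diabetes in general.
- Entry details on the stage of pregnancy and analyses by type may sit in the full protocol or analysis plan, so their absence here is not itself a fault.

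It can also be said that the Background sentence is introductory and does not say only. That softens the disagreement without removing it: eligibility names a type that appears in neither the product description nor the reported planning results, and the article does not say why.

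**Conclusion.** The point holds in a limited form and is minor. The Background and Study population sections describe different populations and need to be reconciled. A condition bound to pregnancy is followed over a fixed 12 weeks and pooled in a model that, as stated, has no term for type. The comparison remains unbiased and the sample size arithmetic is correct. What may be lost is precision and, only if the app effect is smaller in this group, some of the pooled effect.

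The size of that loss rests on assumed shares and effects. Over shares of 5 to 20% and gestational effects of 0 to 0.30 SD, unadjusted power lies between 61% and 80%, and baseline adjustment raises every value. One result does not depend on a smaller effect: at shares of 2 to 20%, power of about 6 to 24% in the gestational group alone cannot support a separate conclusion for it.

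**What to change.** - Reconcile the population in the Background with the eligibility in the Study population section, and give the reason for the inclusion and the expected share.
- Add diabetes type, known at entry, as a factor in the primary ANCOVA and in the imputation model. The purpose is precision; this does not remove dilution.
- Pre-specify the primary analysis repeated in type 1 and type 2 only, to show whether dilution occurred.
- State that the pooled result does not by itself support a claim for gestational diabetes, and that any such claim rests on that group's own estimate and interval.

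The cost is wording and one extra analysis on data already collected. Neither the sample size nor the trial's conduct need change. The downside is that any claim for gestational diabetes becomes explicitly limited.

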### Randomization, sequence generation, and blinding

Randomization will be performed by a computer-generated randomization sequence (Research Randomizer [32]), assigning participants to the interventional or control group in a 2:1 ratio, by block randomization with an initial block size of six and three for subsequent participants. Study centers will receive concealed envelopes with the randomization results for each participant separately. The respective envelope will be opened by the study staff at the first study visit of the participant, and the participant will be allocated accordingly. Due to the nature of the intervention, blinding of participants and study centers providing the intervention will not be possible.

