### Procedures

As depicted in Fig. 1, our study will comprise a 12-week study period that starts and ends with study visits for baseline and follow-up examinations. At study visit 1, participants will be allocated to the study groups according to randomization after informed consent is given. Blood glucose meters from all participants will be read out. Participants of the interventional group will download both the mySugr PRO application (mySugr GmbH, Austria) and the application for mobile EMA capturing time-varying real-life experience (mEMA, ilumivu, USA). Applications will be used via pseudonymized study accounts. Baseline examination at visit 1 will then involve the collection of blood glucose data and the completion of questionnaires on patient-reported outcomes (PRO, see below). Blood glucose data comprise the self-monitored average glucose levels, the corresponding percentages of hypoglycemic (< 70 mg/dl; < 54 mg/dl), euglycemic (70–180 mg/dl), and hyperglycemic (> 180 mg/dl) values, as well as the last documented or routinely assessed HbA1c. During the 12-week study period, participants of the interventional group will use mySugr PRO for diabetes self-management, while control patients will continue with their present mode of self-management. Additionally, participants of the interventional group will daily report their real-world experience via mEMA, both at the beginning and at the end of the interventional phase over a period of 10 days each. Follow-up examination at visit 2 will assess the same data as the baseline evaluation at visit 1, extended by an additional questionnaire on the perceived quality of the intervention and treatment satisfaction (interventional group). Adverse events and serious adverse events will be documented throughout the study. There will be no provisions for ancillary and post-trial care, and there will be no post-trial compensation since we expect no harm due to trial participation.

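### Small fixed 2:1 blocks (six, then three) with envelopes opened by unblinded site staff could make about a third of allocations deducible, if blocks are per centre and staff know the sizes

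*Protocol article*

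**What the plan says.** The section Randomization, sequence generation, and blinding of the protocol article describes a computer-generated sequence with two app allocations for each control allocation. The sequence is built "by block randomization with an initial block size of six and three for subsequent participants". On the mechanism it says: "Study centers will receive concealed envelopes with the randomization results for each participant separately". On who opens them, it says: "The respective envelope will be opened by the study staff at the first study visit of the participant". It also states that "blinding of participants and study centers providing the intervention will not be possible".

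The Procedures section says that "participants will be allocated to the study groups according to randomization after informed consent is given". The Study design section gives the expected centre size: "Approximately 50 study centers will take part in this study with approximately 9 participants each".

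Three things are not stated: that each centre has its own blocks, that sites are told the block sizes or kept from them, and that the sizes vary at random. The Discussion treats lack of blinding as a limitation but does not take up the predictability of the next allocation.

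**The concern.** A sealed envelope hides an allocation only while it cannot be worked out from those already seen. In a block of two app places and one control place, once the control has been drawn the rest must be app, and after two app allocations the third must be control. Staff who open the envelopes in an unblinded trial see that history.

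Someone who knows the next arm can choose whom to approach and when. Allocating after consent stops a person opening the envelope before the participant has agreed, but it does not stop staff timing the approach. The primary endpoint, PAID, is self-reported by unblinded participants, so motivation or affinity for apps could plausibly affect it. The planned analysis of covariance uses baseline data as the covariate, so it corrects only for the part of the selection that the baseline measurement captures.

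**Working it through.** **The plan's own figures.** The article gives no predictability figure to reproduce. Its sample size does reproduce: with an "expected effect size of 0.3 standard deviations", two-sided alpha 0.05 and 2:1 allocation, the noncentral t calculation gives 80.2% power at 264:132 = 396, and 396 / 0.85 = 465.9, so 466. Nothing below changes these numbers.

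**Inputs.** Ratio 2:1, first block six (4 app, 2 control), later blocks three (2 app, 1 control), all from the randomization section. About nine participants per centre, from Study design; 9 = 6 + 3. Two assumptions are added: blocks are per centre, and staff know or infer the sizes.

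**Determined places per block.** A place is determined when the block has only one arm left. With a app and b control places in random order, the expected number is a/(b+1) app places plus b/(a+1) control places.

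- Block of six: 4/3 + 2/5 = 1.333 + 0.400 = 1.733, and 1.733/6 = 28.9%. Enumerating the 15 orders agrees: 8 have one determined place, 4 have two, 2 have three and 1 has four, so (8 + 8 + 6 + 4)/15 = 26/15.
- Block of three: 2/2 + 1/3 = 1.000 + 0.333 = 1.333, and 1.333/3 = 44.4%.

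**Nine-participant centre.** (1.733 + 1.333)/9 = 3.067/9 = 34.1%. By arm: app (1.333 + 1.000)/6 = 38.9%; control (0.400 + 0.333)/3 = 24.4%. Applied to 466 participants, this is about 159.

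**Other completed centre sizes** (one block of six, then threes):

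| Participants | Determined |
|---|---|
| 6 | 28.9% |
| 9 | 34.1% |
| 12 | 36.7% |
| 15 | 38.2% |
| 18 | 39.3% |

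**Best guess.** Guess the arm with more places left, and count a tie as half. The expected number correct is 67/15 = 4.467 in the block of six and 7/3 = 2.333 in the block of three, so 6.8/9 = 75.6%. Always guessing app is right 66.7% of the time.

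**Possible bias.** Suppose staff at every centre use every determined place and shift prognosis by s SD, in opposite directions in the two arms. The difference between arms is then s × (0.389 + 0.244) = 0.633 s, before any baseline adjustment. The documents give no value for s, so a range is shown:

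| Assumed s | Bias |
|---|---|
| 0.05 SD | 0.03 SD |
| 0.10 SD | 0.06 SD |
| 0.25 SD | 0.16 SD |

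If only one centre in five behaved this way at 0.25 SD, the bias would be 0.158/5 = 0.03 SD.

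**With random block sizes.** For nine participants, sizes equally likely, and staff who know the set of sizes but not the order, the determined share is 8.1% (3 or 6), 6.7% (6 or 9) or 2.8% (3, 6 or 9).

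**The case against.** - **Per-centre blocks are inferred.** The article never states them, and nine per centre is an approximate average. With one trial-wide list, 44.2% of positions would be determined in principle, but staff at one centre would not see the other centres' allocations and could not use this fully. This stands as a condition. The inference is still strong, because envelopes go to centres and nine is exactly six plus three.
- **Staff knowledge is not documented.** Withholding block sizes from sites is the kind of detail a condensed article leaves to the full Clinical Investigation Plan, which is not shown. This also stands as a condition. A reader might infer that concealment fails; the documents do not support that. The envelopes are described as concealed, and about two thirds of allocations remain undetermined even with full knowledge.
- **Publication timing.** A reader might infer that the sizes were made public while centres were still recruiting. The Trial status section shows only that the text was written before the expected end of recruitment on May 31, 2022. The document as shown gives no publication date.
- **Size of the bias.** A reader might take 0.16 SD, about half the planned 0.3 SD effect, as the likely bias. That figure needs one chosen shift, used at every centre in one consistent direction, with no reduction for baseline adjustment. The direction is open too: steering keen patients to the app would favour it, while steering more distressed patients there would tend to raise follow-up PAID and work against it.
- **Consent before allocation** is a real safeguard. It narrows the route for selection but does not close it.

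None of this alters the stated choice of small, fixed blocks.

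**Conclusion.** The point holds in conditional form. If blocks are per centre and staff know or infer the sizes, about 34% of allocations (29% to 39% for centres of 6 to 18 participants) are determined before the envelope is opened. Concealment is then weakened and selection bias is possible. How large any bias would be, and which arm it would favour, cannot be established from the documents; the range in the working shows only how it scales with an assumed shift. Because the article fixes the block sizes, this is a weak design choice and not an omitted detail. It is a cheap improvement, held with moderate confidence. The sample size is unaffected.

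**What to change.** For all envelopes not yet issued, generate a new list centrally with block sizes that vary at random within each centre, for example 3, 6 and 9, and do not disclose the scheme to sites. At a nine-participant centre this lowers the determined share from 34.1% to 2.8%, even if staff know which sizes are in use.

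The cost is a new randomization list, replacement envelopes and slightly looser arm balance within centres. The planned 396 evaluable and 466 recruited participants do not change.
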